# Scopolamine augmentation of a newly initiated escitalopram treatment for major depressive disorder: study protocol for a randomized controlled trial

**DOI:** 10.1186/s13063-018-3132-3

**Published:** 2019-01-09

**Keywords:** Scopolamine, Major depressive disorder, Efficacy, Randomized controlled trial

## Abstract

**Background:**

Major depressive disorder (MDD) is a prevalent and disabling disorder that can lead to heavy individual, familial, and societal burdens. Although pharmaceutical interventions still play an essential role in therapeutic measures, limitations, including effects that are delayed for weeks, are noteworthy. Antidepressants with rapid efficacy and acceptable tolerance have been investigated for many years; rapid antidepressant effects and promising clinical applications have been obtained with intravenous and oral scopolamine. This study aims to evaluate the efficacy of repeated intramuscular scopolamine as an add-on treatment to escitalopram.

**Methods:**

This is a single-center, saline-controlled, double-blind, three-armed, randomized trial. Sixty-six participants diagnosed with MDD will be recruited at Beijing Anding Hospital and randomly assigned to one of three groups: a high-dose intramuscular scopolamine augmentation group; a low-dose intramuscular scopolamine augmentation group; and a placebo control group. Our primary endpoint is improvement in the 17-Item Hamilton Rating Scale for Depression (HRSD17) score from the baseline (at least a 20% reduction). Prespecified secondary endpoints include response rates and remission rates as well as changes in the total or subscale scores between the baseline and week 4.

**Discussion:**

This study will provide the first insight regarding the rapid antidepressant efficacy and tolerability of an intramuscular scopolamine add-on to the usual treatment in Chinese MDD patients. The first discussion concerns whether augmentation can accelerate early antidepressant efficacy. A pilot study of intramuscular scopolamine is performed.

The limitations of this study include its small sample size and it being a single-center study, suggesting the need for further confirmation with trials enrolling larger populations.

**Ethics and dissemination:**

The study protocol and all related materials have been approved by the Institutional Ethics Committee of the Beijing Anding Hospital (No. 2016–106, Beijing, China). The findings will be disseminated through peer-reviewed journals and at national and international conferences.

**Trial registration:**

ClinicalTrials.gov, NCT03131050. Registered on 18 April 2017.

**Electronic supplementary material:**

The online version of this article (10.1186/s13063-018-3132-3) contains supplementary material, which is available to authorized users.

## Background

Major depressive disorder (MDD) is a prevalent and disabling condition with a high frequency of non-recovery and recurrence, leading to substantial mortality and morbidity [1–3]. According to the new World Health Organization (WHO) report, the proportion of the global population with depression is estimated to be 4.4% in 2015. In China, > 54 million people (4.2% of the population) suffer from depression [4]. Although antidepressants are the main treatment for MDD, biweekly doses are the minimum requirement for full treatment to be efficacious. Despite the availability of a wide range of antidepressant drugs, clinical studies have indicated that approximately one-third of patients with MDD fail to respond to first-line antidepressant treatment, even if the drugs are used at adequate dosages and durations. Thus, there is an urgent need to develop novel and improved drugs to treat depression [5].

Clinical studies have identified two different classes of drugs with rapid antidepressant action in patients with depression: ketamine, a non-competitive glutamate N-methyl-D-aspartate (NMDA) receptor antagonist [6–8]; and scopolamine, a non-selective acetylcholine muscarinic receptor antagonist [9–12]. Scopolamine has been shown to produce rapid and robust antidepressant effects on current MDD and bipolar disorder patients [9, 13].

In 1991, Gillin discussed the effect of intramuscular injections of scopolamine on depression. In that study, depressive symptoms appeared to improve, but the effect was not significant [13]. In 2006, Furey and Drevets conducted a series of randomized, controlled, double-blind, and crossover clinical trials to determine the antidepressant effects of scopolamine. The results showed that both depressed and bipolar patients demonstrated a rapid and consistent reduction in their Montgomery-Asberg Depression Rating Scale (MADRS) scores by three days after the first infusion. At the end of the trial, nearly two-thirds of the patients improved markedly, in whom half of the symptoms disappeared completely, and the improvement effects lasted for two weeks after the last infusion [9, 11, 12, 14]. In addition to intramuscular and intravenous injections, the antidepressant effect of oral scopolamine has also been discussed; the researchers found that scopolamine and citalopram had an acquired combined effective rate in patients with depression and that citalopram elicited no significant difference regarding the onset time of the antidepressant effects [14, 15].

Previous studies of intramuscular, intravenous, and oral scopolamine have shown some antidepressant effects that have promising clinical applications, but those studies focused on intravenous scopolamine; this study will use the method of intramuscular injections. Compared with intravenous injections, the use of intramuscular injections for the treatment of patients is more convenient and has better acceptability. Although intramuscular injections of scopolamine were shown to be effective in only one of the previous studies, there were limitations in that study including the small number of cases and gender bias [13]. Therefore, we need to improve the program to further explore the efficacy of intramuscular injections.

Due to the lack of a known effective dose of intramuscular scopolamine in previous studies, we designed a dose-finding study using a scopolamine dose range that was previously associated with cognitive effects but without toxic effects such as delirium. In reference to the static drops in scopolamine antidepressant effective doses and to the recommended dose range of scopolamine injection specification, we chose a high-dose group (0.6 mg/day) and a low-dose group (0.3 mg/day). To ensure that the drug clearance was complete before the next injection, we designed the trial protocol to include morning and afternoon intramuscular injections each time; the treatment interval was 6 h.

Most of the trials were crossover studies and only used a single intravenous injection, limiting the generalizability of the findings. Previous studies have shown a rapid antidepressant effect of scopolamine; therefore, we added antidepressant treatment to see if scopolamine could accelerate the onset of antidepressant drugs. Our team’s research showed that single-dose intravenous ketamine augmentation by escitalopram was safe and effective in the treatment of severe MDD, showing the promise of speeding up early oral antidepressant efficacy [16]. To date, the effects of add-on scopolamine on currently available antidepressants have not been examined and it remains unknown whether concurrent initiation or oral antidepressant treatment with intramuscular scopolamine may increase antidepressant efficacy. Taking into account that the antidepressant effect of scopolamine is fast but not sustained, the focus of our study is on how to use scopolamine’s antidepressant effect to help patients with depression symptoms improve in the early stage. Therefore, we aimed to determine the antidepressant effects and safety of low-dose or high-dose single intramuscular scopolamine infusions, which were combined with escitalopram initiation in MDD.

## Objectives

This study is designed to verify whether the augmentation of intramuscular scopolamine may accelerate the efficacy of antidepressant treatment.

## Methods

### Study design

The trial is a single-center, double-blind, three-arm randomized trial with four-week follow-ups at Beijing Anding Hospital, which is affiliated with Capital Medical University. The protocol is reported as following the SPIRIT checklist (see Additional file 1). The actual study start date was 15 March 2017 and the completion date is 31 August 2018.

### Participants

All patients diagnosed at the outpatient clinics of Beijing Anding Hospital between 1 February 2017 and 31 August 2018, will be identified as potential participants and be invited to participate in this study.

#### Inclusion criteria

Aged 18–45 years;diagnosis of MDD according to the Diagnostic and Statistical Manual of Mental Disorders, Fourth Edition (DSM-IV) criteria;a total score of the 17-Item Hamilton Rating Scale for Depression (HRSD17) ≥ 20;duration of the index episode is ≥ 4 weeks.

#### Exclusion criteria

Current enrollment in, or discontinuation within the last 30 days from, a clinical trial involving off-label use of an investigational drug;other disorders in DSM Axis I;organic mental diseases, including mental retardation;history of any clinically significant disease, including cardiovascular, hepatic, renal, respiratory, hematologic, endocrinologic, or neurologic disease or clinically significant laboratory abnormalities that are not stabilized or are anticipated to require treatment during the study;exposure to different formulations and generic agents of investigational drugs during the three months before screening;a positive pregnancy test or breast feeding;women of childbearing potential without appropriate birth control measures;antipsychotics or mood stabilizers within the five days before screening;allergy to or lack of response to escitalopram;electroconvulsive therapy (ECT) or modified ECT within the three months before screening;hypersensitivity to anticholinergic agents;smoking;significant risk of suicide, as evidenced by scoring 3 or 4 for HRSD17 Item 3, and risk of self-harm behaviors as ascertained by the investigator after inquiry.

### Interventions

Individuals are equally and randomly allocated to three treatment regimens groups that are different only for the first three days: (1) the high-dose group receives 0.3 mg of intramuscular scopolamine twice daily; (2) the low-dose group receives 0.3 mg of scopolamine in the morning and saline in the afternoon; and (3) the saline-controlled group is injected with intramuscular saline twice daily. After the first three days of add-on injections, the participants receive monotherapy with a fixed dose of oral escitalopram for the remaining 25 days. Injections are administered at 09:00 and 15:00 by the research nurse.

All the individuals stay in the emergency wards during the first three days and receive clinical visits on the 4th, 7th, 14th, and 28th day from the first injection.

See “Fig. 1 Study flow chart” for a detailed overview of the research procedure.

**Fig. 1 Fig1:**
[figure not shown]
Study *flow chart*

#### Drug/therapy combination

Drug or therapy combinations are permitted in cases of preset conditions as follows: (1) if participants suffer from insomnia, sleep aides (zolpidem [≤ 10 mg daily], zopiclone [≤ 7.5 daily], or zaleplon [≤ 10 mg daily]) are permitted for up to seven days total throughout the study and in any case of ineffectiveness, a switch can only occur between those on the list; and (2) administration of lorazepam is permitted for short-term management of treatment for adverse events (AEs), such as anxiety and agitation, up to a maximum of 3 mg/day. Benzodiazepines must not be administered within the 8 h before scheduled efficacy and safety assessments.

### Outcomes

The primary outcome for this study is improvement of the HRSD17 score from the baseline to 28 days (at least a 20% reduction). Secondary outcomes are response rate (a 50% decrease in HRSD17 score from baseline), remission rate (HRSD17 score ≤ 7), changes in HRSD17, MADRS, Quick Inventory of Depressive Symptomatology Self Report 16-Item (QIDS-SR16), Generalized Anxiety Disorder 7-Item (GAD-7), Young Mania Rating Scale (YMRS), and Clinical Global Impression (CGI) Scale scores throughout the trial.

The Chinese version of the HRSD17 has satisfactory psychometric properties in terms of validity and reliability. The internal reliability and the validity are good (Cronbach alpha = 0.714; *r* = − 0.487) [17]. The scale is widely used to measure the efficacy of antidepressant medication in clinical trials, as HRSD17 is more sensitive to change on retesting [18, 19]. The MADRS is an interviewer-rated instrument, comprising 10 items, each measured on a 6-point scale (scores range from 0–60 with higher scores depicting greater symptom severity). It has been found to be a robust and psychometrically sound measure of depressive symptomatology [20]. CGI was used to assess change in symptoms from baseline to endpoint. QIDS-SR16, a measure of depressive symptom severity derived from the Inventory of Depressive Symptomatology, has highly acceptable psychometric properties (Cronbach alpha = 0.70; *r* = 0.61) which supports the usefulness of this brief rating of depressive symptom severity in both clinical and research settings [21]. There are 16 items in the adult versions of the QIDS-SR16 measuring the nine criterion symptom domains (sleep, sad mood, appetite/weight, concentration/decision making, self-view, thoughts of death or suicide, general interest, energy level, and restlessness/agitation) that define a major depressive episode according to the DSM-IV. GAD-7 is a self-reported questionnaire for screening and for measuring the severity of generalized anxiety disorder. Cronbach’s α coefficient and an area under the receiver operating curve for the GAD-7 are 0.888 and 0.974, respectively [22]. YMRS is an 11-item multiple choice diagnostic questionnaire used to evaluate manic symptoms. The CGI was developed for use in clinical trials to provide a brief, stand-alone assessment of the clinician’s view of the patient’s global functioning before and after initiating a study medication. The CGI comprises two companion one-item measures evaluating the following: (1) severity of psychopathology on a scale of 1 to 7; and (2) change from the initiation of treatment on a similar 7-point scale.

### Sample size

According to the published research and clinical expectations, we estimated the median time from the baseline to early improvement (at least a 20% reduction of HRSD17 score) of scopolamine plus escitalopram is 6.4 days and the four-week remission rate is 92.3%. The median time from the baseline to early improvement of placebo plus escitalopram treatments is 26.5 days and the four-week remission rate is 57.1%. Considering the time to early improvement, which is fitted to an exponential distribution, and assuming a power of 80% with a two-sided significance of 0.01, a minimal sample size of 54 was calculated using survival (time to event) modules. A common method for testing the proportional hazards assumption is to include a time interaction term to determine if the hazard ratio changes over time, since time is often the culprit behind non-proportionality of the hazards. Evidence that the group*time interaction term is not zero is evidence against proportional hazards. Assuming an attrition of 10%, at least 66 participants are planned.

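### The two placebo inputs in the sample-size section cannot both hold: the 26.5-day median implies 51.9% improved by day 28, below the stated 57.1% remission

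*Protocol article*

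**What the plan says.** The Sample size section of the protocol article gives two planning figures per arm. For the active combination: "we estimated the median time from the baseline to early improvement (at least a 20% reduction of HRSD17 score) of scopolamine plus escitalopram is 6.4" (unit: days). Remission at four weeks in that arm is put at 92.3%. For the control: "The median time from the baseline to early improvement of placebo plus escitalopram treatments is 26.5 days and the four-week remission rate is 57.1"%.

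The model is given next: "Considering the time to early improvement, which is fitted to an exponential distribution". The error rates are fixed by "assuming a power of 80% with a two-sided significance of 0.01". The result is that "a minimal sample size of 54 was calculated using survival (time to event) modules", raised to 66 for 10% attrition. The section does not say what part, if any, the two remission rates play in the calculation.

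Two definitions elsewhere matter. The Outcomes section defines remission by a score threshold, "remission rate (HRSD17 score ≤ 7"), and follows the primary outcome to 28 days. The Inclusion criteria require "a total score of the 17-Item Hamilton Rating Scale for Depression (HRSD17) ≥ 20".

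**The concern.** Remission is a much harder event than early improvement. A patient who enters at 20 and ends at 7 has fallen by 13/20 = 65%, and a higher entry score makes the fall larger. Anyone in remission at four weeks has therefore already passed the 20% mark. In each arm, the 28-day improvement probability must be at least the four-week remission rate. The placebo figures break that rule.

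The median and the model are the inputs to the only justification given for the sample size. The effect they imply is also the natural reading of the expected effect in the Monitoring section, where the sample size may be raised at the interim if the treatment effect proves smaller than expected. If the placebo median is the faulty figure, both the stated power and that benchmark are too favourable.

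**Working it through.** **Inputs.** Medians 6.4 and 26.5 days, exponential times, power 80%, two-sided 0.01, minimal N 54, attrition 10%, planned N 66 and remission rates 92.3% and 57.1% (Sample size); 28-day horizon (Outcomes); 1:1:1 allocation (Randomization section), hence 18 per arm at 54 and 22 per arm at 66.

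**Step 1: reproduce the plan's figure.** With P = 1 − 2^(−28/median):
- Active: 1 − 2^(−28/6.4) = 0.952.
- Placebo: 1 − 2^(−28/26.5) = 0.519.
- HR = 26.5/6.4 = 4.14, and ln HR = 1.421.
- n per arm = (2.576 + 0.842)² × (1/0.952 + 1/0.519) / 1.421² = 17.2, so 18 per arm and 3 × 18 = 54.

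This matches the stated minimum from the medians alone; no remission rate is used. Other standard formulas on the same inputs give other totals (48 by Schoenfeld, 66 by Freedman), so the formula is inferred, not stated. Power at 18 per arm is 82.1% by this log-hazard formula and 86.0% by Schoenfeld.

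**Step 2: compare improvement with remission.**

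| Arm | Improved ≥20% by day 28 (implied) | Remission at four weeks (stated) | Compatible? |
|---|---|---|---|
| Scopolamine | 95.2% | 92.3% | Yes |
| Placebo | 51.9% | 57.1% | No, short by 5.2 points |

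**Step 3: if the 26.5-day median is right.** HR 4.14 and N = 54 are unchanged. Only the 57.1% is affected.

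**Step 4: if 57.1% is right and the active median stays at 6.4 days.** Placebo improvement is then at least 57.1%.
- Placebo hazard at least −ln(0.429)/28 = 0.0302 per day, so the median is at most 0.693/0.0302 = 22.9 days.
- HR at most 22.9/6.4 = 3.58.
- n per arm = 11.68 × (1/0.952 + 1/0.571) / (ln 3.58)² = 20.1, so 21 per arm and N = 63, or 70 after 10% attrition.

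| Patients per arm | Log-hazard power | Schoenfeld power |
|---|---|---|
| 18 (N = 54) | 74.5% | 77.8% |
| 19.8 (66 less 10%) | 79.3% | 82.3% |
| 22 (N = 66) | 84.1% | 86.8% |

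These are upper limits for this branch, because they assume that every placebo improver remits.

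**Step 5: sensitivity, on assumed values.** Suppose 65% of placebo patients improve by day 28 (an assumption; the article gives no such figure) and the active median stays at 6.4 days. The placebo median is then 28 × 0.693/1.050 = 18.5 days and HR is 2.9. Power at 22 per arm is about 70% (log-hazard) to 72% (Schoenfeld). If instead both medians shorten in proportion, HR stays at 4.14. Schoenfeld power at 22 per arm is then 94–97% for placebo improvement between 57.1% and 80%.

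**The case against.** The strongest reply is that a conflict between two inputs does not show which is wrong. The 54 follows from the medians alone, so a mislabelled 57.1% would leave the calculation intact. That stands. A reader might infer that the hazard ratio and the 80% power are simply overstated, but the article supports this only on condition that 57.1% is the correct figure.

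Second, the contradiction needs the exponential form. A 26.5-day median by itself requires only that half have improved by then, and with visits on days 4, 7, 14 and 28 (Interventions) observed improvement need not follow a smooth curve. This is true but of limited help. The exponential is the section's own model. Without it, at least 7.1% of placebo patients would have to go from under 20% to at least 65% improvement in the 1.5 days after the median, and every earlier improver would have to remit.

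Third, a reader might infer that both pairs really describe one stricter event. The figures do not support this. Under an exponential model, 57.1% at day 28 needs a median of 22.9 days, not 26.5, and 92.3% needs 28 × 0.693/2.564 = 7.6 days, not 6.4. Neither pair fits a single event.

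Fourth, in the one alternative bounded by the article's own figures, the planned 66 roughly keeps 80% power, and the interim re-evaluation offers some protection. Both points stand and limit the size of the problem. They do not make the inputs consistent.

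**Conclusion.** The placebo median and the placebo remission rate are incompatible under the article's own model and definitions, by 5.2 percentage points. The section is wrong as written, and one of the two figures must be changed or redefined. Calling 57.1% the improvement rate instead would not resolve it, because it would still exceed 51.9%.

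The effect on power is conditional. It is nil if the 26.5-day median is right. If 57.1% is right and the active median is kept, the hazard ratio is at most 3.58 instead of 4.14. Power at the minimal 54 is then at most about 75–78%, and about 79–82% with 66 enrolled and 10% attrition. A larger loss requires that more placebo patients improve than remit while the active median stays at 6.4 days. That is plausible, but no figure in the article fixes its size, so a claim that the trial is severely underpowered is not supported. All power figures assume a pairwise comparison of one active arm with placebo, exponential times and censoring at day 28.

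**What to change.** In the Sample size section:

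1. State the source of each median and each rate, and the event it describes (20% reduction, response or remission).
2. Make the placebo median and 28-day rates consistent, so that improvement is at least as frequent as remission under the stated model.
3. Recompute the hazard ratio and name the formula used.
4. Restate the power of the planned 66, before and after 10% attrition, with the reconciled inputs and a labelled sensitivity range for placebo improvement. Say whether the active median is held fixed or moves with it.

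In the Monitoring section, use the reconciled effect as the expected effect for the interim re-evaluation of sample size.

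The cost is a rewording and a short recalculation. The correction itself requires no extra patients, but the stated power may become less favourable.

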### Recruitment

Patients will be mainly recruited via referral from psychiatrists in the outpatient department. At the screening visit, the trained research investigators and blind raters collect and make judgments regarding eligibility. The Chinese version of the MINI is used to confirm that the DSM-IV criteria for MDD are met and to assess the exclusion criteria. Vital signs, weight, height, physical examination, ECGs, and clinical safety laboratory tests are taken sequentially.

